For several years a growing number of studies have explored the effects of non-invasive brain stimulation in patients with aphasia following left hemisphere strokes. These studies rely on the assumption that weak electrical currents can interact with neural networks subtending language and promote neural plasticity, allowing short-term modulations, and eventually clinical recovery. Within these language-related networks, left and right homotopic regions are connected via transcallosal connections [28, 29] which, according to the principle of inter-hemispheric inhibition, tend to convey mutual net inhibitory influences [30]. The use of non-invasive brain stimulation in left hemisphere stroke aphasia relies on three potential mechanisms or combinations thereof [31, 32]: (1) the use of left-excitatory (anodal tDCS or high-frequency TMS) stimulation on left hemisphere language systems to reactivate language processes implemented by peri-lesional regions; (2) the delivery of right-inhibitory (cathodal tDCS or low-frequency TMS) stimulation to reduce the inhibition that right hemisphere systems exert on the left dominant language network and (3) the delivery of right-excitatory stimulation to activate potential language contributions of right hemisphere networks. The most promising clinical outcomes on language disabilities have been achieved from studies adopting the first two approaches using either TMS (e.g., see [33–36]) or tDCS (e.g., see [37–39]). Beneficial effects have been shown either transiently with single-session applications, or as longer-lasting impacts (> 6 months) following periodical stimulation sessions across several days, probably related to stimulation-induced neuroplasticity [34, 40].

Non-invasive brain stimulation has also been used with relative efficacy in Alzheimer’s disease by targeting the left and/or right dorsolateral prefrontal cortex [41, 42]. In PPA, including SD (or sv-PPA), two small-cohort studies have suggested encouraging results with both TMS and tDCS [43, 44]. However, the authors did not target language-specific brain regions and the small number of patients precluded a counterbalanced study design. In addition, left-excitatory versus right-inhibitory TMS or tDCS have not been systematically evaluated to reveal the most efficient strategy in aphasia of neurodegenerative origin.

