The primary endpoint of the *STIM-SD* protocol is to evaluate the potential therapeutic efficacy of multiday tDCS (10 days) on language/semantic performance in patients with SD (see the section “Language/semantic tasks” – the semantic association task). In addition, we will also (1) assess the time course of potential language/semantic improvement through the application of four follow-up time points; (2) assess neuroimaging biomarkers (PET and MRI) that could reflect stimulation-induced neuroplasticity and response to stimulation; (3) compare the effects of left-anodal and right-cathodal tDCS to define the most efficient stimulation modality; (4) identify biomarkers that could individually predict tDCS impact and (5) improve the understanding of the semantic roles of the left and right ATL and their potential structural connectivity, contributing to the definition of anatomic-functional models of semantics.

The protocol has been approved by the local Ethics Committee and is registered in ClinicalTrials.gov with the identifier NCT03481933 and the study title “‘Evaluation of a Transcranial Stimulation with Direct Current on Language Disorders in Semantic Dementia (STIM-SD)”*.* Written informed consent is obtained from all patients and healthy subjects before the onset of any of the study procedures. All research protocol visits take place at the same site, the Pitié-Salpêtrière Hospital. Two additional centers contribute to the protocol by recruiting patients with SD.

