To identify biomarkers that could individually predict an efficient tDCS impact, 3D-T1 and DTI sequences will be explored and individual computational models of tDCS current will be produced. Structural 3D-T1 MRI data will be studied using surface-based cortical thickness analysis. An ROI will be defined in the ATL and cortical thickness values at baseline between a group of eventual “responders” (mean improvement of 15% in correct responses in the SA test) and “non-responders” to the stimulation will be compared using a general linear model. Diffusion MRI data will be studied using ROI analysis of DTI metrics. Fractional anisotropy (FA) and mean diffusivity (MD) maps will be calculated and the integrity of a set of anatomical white matter tracts will be assessed (FA and MD measures in each tract). The tracts analyzed will include bilaterally the inferior longitudinal fasciculus, the uncinate fasciculus, the superior longitudinal fasciculus, the inferior frontal-occipital fasciculus and different corpus callosum tracts connecting the left and right temporal lobes. This will allow a detailed anatomical analysis of white matter fiber tracts and compare their status between a possible group of responders and non-responders. The individual computational models of tDCS current magnitude will be used to identify which anatomical characteristics influence the amount of current reaching the target in the brain and if such measure can help predict the response to stimulation. Finally, the analyses of DTI data will also allow us to explore connectivity between the left and right ATL to improve the understanding of the semantic roles of each of these regions while contributing to the definition of anatomic-functional models of semantics.

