In addition, baseline structural data (3D-T1 cortical thickness, DTI fiber tract analyses) and individualized models of tDCS current magnitude and distribution will be fundamental in understanding which anatomical features of our cohort most influence treatment efficacy, how the amount and spreading of electric current in the brain will impact individual clinical outcomes and possibly define a profile of patients that in the future would most benefit from tDCS.

Within neurodegenerative diseases specifically affecting language, SD is the most frequent variant of primary progressive aphasia [2], which contributes to the feasibility of the project in terms of patient recruitment. In the same vein, our National Reference Center for Rare or Early Onset Dementias provides a unique opportunity to recruit a large and homogeneous cohort of patients with SD. The active patient files on patients with early-stage SD in the three recruiting centers contained more than 20 patients with SD per year in 2013, 2014 and 2015. This shows that the total number of 60 patients with SD can be reached in the current project.

A potential tDCS treatment would be easily applicable, inexpensive and renewable when therapeutic effects disappear due to disease evolution. Significant effects of repetitive tDCS on language/semantics would also open an avenue for future tDCS trials targeting language non-related cortical regions such as areas subtending episodic memory, which is damaged, for example, in Alzheimer’s disease. More generally, the protocol might improve the understanding of neuroplasticity and its modulation through inhibitory and/or excitatory tDCS-driven cortical impact, while providing a rationale for appropriate stimulation modalities and for identifying brain regions likely to demonstrate relevant plasticity. Such insights could prove important for both tDCS and TMS trials, and their combination with behavioral language rehabilitation strategies, which might further enhance plasticity-related modulation.

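### For the 3D-T1 and DTI markers the aim is prediction in the individual patient, but the stated analysis is a responder versus non-responder comparison, which cannot show it

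*Protocol article*

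**What the plan says.** Among the secondary aims listed under Study design, the fourth is to "identify biomarkers that could individually predict tDCS impact". The Data analyses section takes this up for the structural sequences ("To identify biomarkers that could individually predict an efficient tDCS impact, 3D-T1 and DTI sequences will be explored") and then names the methods.

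- **Cortical thickness (3D-T1).** An ROI is placed in the ATL. Its baseline thickness in responders and non-responders "to the stimulation will be compared using a general linear model". A responder is described by a "mean improvement of 15% in correct responses in the SA test".
- **Diffusion (DTI).** FA and MD are measured in a list of tracts, most of them bilaterally, in order to "compare their status between a possible group of responders and non-responders".

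Neither item says which arms supply the responders and non-responders, and neither gives a measure of discrimination, classification or validation.

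A third strand is handled differently. Under Computational models of tDCS current magnitude and distribution, modelled current is to be correlated with each patient's change in SA score.

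The Discussion says that the baseline structural data and the current models together should "possibly define a profile of patients that in the future would most benefit from tDCS".

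**The concern.** A comparison of groups starts from the outcome and asks whether the marker differs on average. Individual prediction starts from one patient's marker value and asks how well it forecasts that patient's outcome. A p-value answers the first question. The second needs a measure of prediction, obtained in data not used to find the marker. The plan states the second question and names a method for the first.

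The Introduction also gives the two active arms different rationales. One is to reactivate left-hemisphere language processes. The other is "to reduce the inhibition that right hemisphere systems exert on the left dominant language network". A marker need not matter equally in both, yet the stated comparison has no arm in it.

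What objective 4 can conclude is at stake. A thickness or tract measure could pass the stated test, enter a patient profile, and still sort individual patients poorly.

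**Working it through.** **The plan's own figure.** The article gives no sample size, effect size or power for the marker analysis. Its 20 patients per group relate to the primary endpoint and are not disputed here.

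**Inputs from the article.** Allocation is 20 left-anodal, 20 right-cathodal and 20 sham (Study design), so 40 patients receive active stimulation. The significance level is 5% (Data analyses).

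**Assumptions not in the article.** The marker is normal with equal variance in the two groups. The 40 active patients split 20/20 into responders and non-responders; other splits are shown. No multiplicity correction is applied; a corrected level would raise the smallest significant difference.

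**Step 1: smallest significant standardised difference.** d = t(0.975, n1 + n2 − 2) × √(1/n1 + 1/n2). For 20/20: d = 2.024 × √(2/20) = 2.024 × 0.316 = 0.64.

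**Step 2: what that d means for one patient.** AUC = Φ(d/√2) = Φ(0.453) ≈ 0.67. The proportion misclassified at the midpoint cut, which is the best cut for equal groups, is Φ(−d/2) = Φ(−0.32) ≈ 37%. Chance is 0.50 and 50%.

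**Step 3: other cases.**

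| Case | d | AUC | Misclassified at midpoint cut |
|---|---|---|---|
| 20/20, just significant | 0.64 | 0.67 | 37% |
| 10/30, just significant | 0.74 | 0.70 | 36% |
| 10/10 (one arm alone), just significant | 0.94 | 0.75 | 32% |
| Larger difference, d = 1.0 | 1.00 | 0.76 | 31% |

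In the 10/30 case, calling every patient a non-responder would misclassify 10/40 = 25%, fewer than the 36% at the midpoint cut.

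**Step 4: precision.** By the Hanley-McNeil formula, an AUC of 0.67 from 20 and 20 patients has a standard error of about 0.086. The 95% interval is 0.67 ± 1.96 × 0.086, about 0.50 to 0.84. A marker at the edge of significance is therefore compatible with almost no discrimination and with good discrimination. These figures also take the AUC in the patients in whom the marker was found, which tends to flatter it.

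**The case against.** **The aim is pursued in another way too.** A reader might infer that the whole prediction objective rests on responder comparisons. It does not. Correlating modelled current with SA change uses a continuous outcome per patient and no responder split. That is still an association and not a test of prediction, but the point has to be confined to 3D-T1 and DTI.

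**Pooling of the arms is not stated.** A reader might infer that the two active arms are merged. The text names no arm, and neither includes nor excludes sham. A general linear model can carry arm as a factor, and its terms are commonly settled in an analysis plan that is not shown. What stands is that the comparison, as described, does not separate the arms. A loss of power from pooling cannot be put in figures from the article. It would need an assumed pattern, such as a correlation in one arm and none in the other. It would also have to allow for testing both arms, and for the gain from pooling if the marker works in both.

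**Side is partly covered.** Most tracts are measured bilaterally, and callosal tracts are included. Only the ATL thickness ROI is given without a side.

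**The language is cautious.** The markers are to be explored, the responder group is called possible, and the profile is a hope. Nothing says that a p-value will be announced as a validated predictor. That lowers the stakes. It does not remove the mismatch, because individual prediction is the declared aim and a method that cannot show it is the one named.

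**Conclusion.** The point holds for the 3D-T1 and DTI strands. This is more than detail left to a later document: a method is named, and it answers a different question from the one stated. If 40 patients split 20/20 and the marker is normal, significance alone is compatible with an AUC of about 0.67 and about 37% misclassified. A 10/30 split gives an AUC of about 0.70, and 10 versus 10 about 0.75. The exact figures depend on those assumptions; the conclusion does not.

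It does not follow that the arms are pooled, that a real marker would be missed with any stated probability, or that the objective as a whole has no other analysis. The primary endpoint, the sample size and the main trial conclusion are untouched. The change is worth making because it decides what objective 4 can claim.

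**What to change.** In the Data analyses section:

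1. Choose a small set of markers in advance, for example left ATL thickness, right ATL thickness and one callosal measure. Entering everything is not workable. Two ATL sides plus four bilateral tracts with FA and MD each (4 × 2 × 2 = 16) already give 18 predictors before any callosal tract, in about 40 treated patients.
2. Model continuous 2-week SA change on the marker, with arm as a factor.
3. Report cross-validated R2 or AUC, with its interval, next to any responder versus non-responder difference.
4. Describe the results as group-level associations unless out-of-sample prediction is shown. Where it is shown, give its size. An interval that just excludes no prediction is not enough, since Step 4 shows that an AUC only slightly above 0.67 could meet that rule.

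No new data are needed. The cost is a little more analysis, and prediction figures that will be less favourable than p-values and imprecise at this sample size. If the extra analysis is not wanted, rewording the aim as association costs almost nothing.

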### Computational models of tDCS current magnitude and distribution

There is evidence that the thickness of the skull, the volume of the cerebrospinal fluid in the subdural space and the distance from the targeted region in the brain to the tDCS anode or cathode account for up to 50% of the spatial variation of the electric field strength [61–63]. Kim et al. [64] found that performance improvement in a working memory task correlated with the simulated current magnitude, suggesting that inconsistent behavioral outcomes of tDCS might be partly due to individual anatomical differences.

A computational approach of modeling should allow for defining if and how tDCS current magnitude and distribution in the heads of individuals can differ and how these differences will affect clinical outcomes. Individual computational models will be produced using the open-source tool ROAST [65] to simulate tDCS current magnitude and distribution using the anatomical 3D T1-weighted MRI images of each patient (Fig. 5). Then, correlation will be tested between model-estimated data for current magnitude values and clinical data, specifically the changes in scores in the SA task from baseline to post-stimulation. A region of interest (ROI) will be defined and the mean of the 5% highest electric field values in this region will be obtained for each patient. More specifically, we will define the left anterior/middle temporal lobe as our ROI, because this region is primarily damaged in SD and it is the region targeted during the stimulation. Finally, measures of thickness of the different tissue layers (skin, skull, cerebrospinal fluid volume, gray matter and white matter) and distances between the stimulation target (ATL) and the stimulating electrode will be obtained and regression models will be computed to identify specific features that most influence changes in current magnitudes. This will allow us to identify the characteristics that might influence patients’ responses to tDCS and help predict if an individual patient might benefit from tDCS treatment.

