### Sample size

The primary evaluation criterion is the change over 2 weeks in performance on the SA task. Performance is measured by the percentage of correct responses. The trial will be considered as positive if performances after left-anodal or right-cathodal tDCS are shown to be significantly superior to sham stimulation. The sample size is based on the results of a preliminary study comparing sham stimulation to left-anodal and right-cathodal stimulation in 12 patients [45]. In our pre-therapeutic study, the mean difference in performance improvement between sham and both anodal and cathodal stimulation was about 15% with a standard deviation of 16% and an effect size of 1.464. The difference in mean change between sham stimulation and each of the two other groups is then expected to be 15% of correct responses. The inclusion of 20 patients in each group will provide statistical power of 80%.

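### Structural predictors of tDCS benefit are sought by splitting patients at a 15% gain of their own, with no stated reference to sham, so a predictive marker cannot be told from a prognostic one

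*Protocol article*

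**What the plan says.** Study design lists among the further aims to "identify biomarkers that could individually predict tDCS impact". Data analyses repeats that purpose ("To identify biomarkers that could individually predict an efficient tDCS impact") and gives the method. Baseline cortical thickness in an anterior temporal region is compared between two groups formed after treatment: responders, defined by a "mean improvement of 15% in correct responses in the SA test", and non-responders. The two groups "to the stimulation will be compared using a general linear model". The DTI tract measures are then used to "compare their status between a possible group of responders and non-responders".

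The section on computational models takes another route for modelled current. It correlates current magnitude with clinical data, "specifically the changes in scores in the SA task from baseline to post-stimulation", so there the outcome stays continuous.

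In Sample size, the difference in mean change between sham and each active arm "is then expected to be 15% of correct responses", with a standard deviation of 16%.

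**The concern.** Predicting the impact of tDCS is a question about treatment effect: does the active-minus-sham difference vary with the biomarker? A patient's raw gain does not measure that difference. It adds together any stimulation effect, practice, natural course over the interval, regression to the mean from a low baseline, and the noise of a short two-choice test. A baseline measure related to any of these will differ between high and low gainers whether or not it has any bearing on tDCS. The trial has a randomised sham arm that can remove these components, and the primary and time-course analyses use it. The stated responder comparison does not.

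The cut-off makes this worse, because it sits at the size of the expected mean effect. Patients with the same true benefit would then be divided into two nearly equal groups by noise. At stake is the aim of describing which patients benefit most, which the Discussion presents as a possible result of the baseline structural data.

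**Working it through.** **Inputs.** Cut-off 15% (Data analyses). Expected active-minus-sham difference 15, SD 16, effect size 1.464, 20 per group (Sample size). 26 trials per SA modality, two modalities (Semantic association task). Assumptions, because the article does not give them: mean sham change m, SD of individual change s, true test accuracy, normal distribution of change. Percentages are read as percentage points.

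**1. The plan's own figure.** With two-sided alpha 0.05 and 80% power, n = 2 × (1.960 + 0.842)² × (16/15)² = 17.9, so 18 per group (19 with the t distribution), against 20 stated. The stated n is therefore roughly reproduced if 16 is taken as the between-patient SD of change. The wording leaves this open, and 15/16 = 0.94 is not 1.464. Other values of s are therefore tried: 16/√2 = 11.3 (if 16 is the SD of a difference between two independent changes), 15/1.464 = 10.25, and 8 as a low case.

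**2. Active patients below the cut-off.** If every active patient benefits by exactly 15 points, mean active change is m + 15, and P(gain < 15) = Φ(-m/s).
- m = 0: 50% for any s, which is 20 of 40
- m = +5, s = 16: Φ(-0.3125) = 38%
- m = -5, s = 16: Φ(0.3125) = 62%

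In this scenario all the non-responders have the same true benefit as the responders.

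**3. Reaching the cut-off with no effect (m = 0).** P = 1 - Φ(15/s). The last column divides by 50%. It gives the share of active responders who would have reached 15 points anyway under a constant 15-point benefit.

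| s | 15/s | P(gain ≥ 15), no effect | Share of active responders |
|---|---|---|---|
| 16 | 0.94 | 17.4% | 35% |
| 11.3 | 1.33 | 9.2% | 18% |
| 10.25 | 1.46 | 7.2% | 14% |
| 8 | 1.88 | 3.0% | 6% |

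At s = 16 the no-effect rate is 10.6% for m = -5 and 26.6% for m = +5.

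**4. Test noise alone.** With no true change, the two scores are independent binomials. On 26 items 15% is 3.9 items, so 4 more correct answers are needed (4/26 = 15.4%). On 52 items, both modalities pooled, 15% is 7.8 items, so 8 are needed. Exact probabilities of such a gain:
- 26 items: 5% at accuracy 0.9, 13% at 0.75, 16% at 0.6
- 52 items: 0.7% at 0.9, 4.4% at 0.75, 6.6% at 0.6

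**5. Consequence for the predictor analysis (simulation).** Every active patient benefits by exactly 15 points, so there is nothing to predict. The marker is purely prognostic: in all arms it has an assumed correlation r with change. SD is 16 and sham change 0. Splitting the 40 active patients at 15 and comparing the marker between the halves at the 5% level gives a significant difference in about 33% of trials for r = 0.3 and 75% to 76% for r = 0.5. The arm-by-biomarker test in all 60 patients rejects in about 5% for either r.

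**The case against.** The strongest reply is that this is a condensed article. It does not list the terms of the general linear model or say whether sham patients enter, so a fuller document may contain a sham comparison. That stands against one inference a reader might draw, that the trial has ruled out any contrast with sham. The text does not say so. It does not rescue the method that is stated. Responders are defined by their own gain, and this definition produces the problem whichever patients enter. Reading responders to the stimulation as active patients only does not help either: step 5 uses active patients only.

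A reader might also infer that every predictor analysis dichotomises. That is wrong: modelled current is correlated with continuous SA change. The criticism of the split covers thickness and DTI only. The current analysis does, however, also state no sham reference.

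The figures are conditional, and that objection stands in full. The 15% in Sample size is a difference between arms, while the 15% in Data analyses is a patient's own gain. They coincide only if mean sham change is zero, which the article does not state. The 17% and 35% need 16 to be the SD of individual change. The 13% needs 26 items and 75% accuracy. An unconditional claim that half of those who benefit are mislabelled would go too far.

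Finally, the aim is secondary and cautiously worded, and no patient-selection rule is attached to it. A claim that future patients will be wrongly selected is not supported.

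**Conclusion.** The point holds for the stated cortical-thickness and DTI comparison. A split on own gain, without a sham reference, cannot show that a baseline marker predicts benefit from tDCS. It can only show that the marker goes with short-term change. This conclusion follows from the definition and needs none of the assumed figures.

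Its size depends on assumptions. With sham change near zero, about half of active patients would be called non-responders under a uniform benefit of 15 points (38% to 62% for sham change of +5 to -5 at SD 16). Between 3% and 17% would reach the cut-off without any effect, for an SD of change of 8 to 16. Test noise alone gives 5% to 16% on 26 items, or about 1% to 7% on 52. In the simulated case a prognostic marker was taken for a predictor in one third to three quarters of trials, for assumed correlations of 0.3 and 0.5.

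This is a point to correct in a secondary, exploratory analysis. It does not affect the primary test.

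**What to change.** In all randomised patients, regress the 2-week SA score on baseline SA, arm, biomarker and arm-by-biomarker, with sham as the reference arm. Call a biomarker predictive only on the interaction, and label the result exploratory. Use the same model for modelled current in place of a correlation without a sham reference, with a current value simulated for sham patients as if stimulated. Keep the 15% split as description only. State whether 15% means percentage points or relative change, which SA modality (or both) it uses, and what a mean improvement is for a single patient.

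The cost is a change of wording. Baseline MRI and SA scores are already planned in all three arms, so no new data are needed. The downside is precision: with 20 per arm the interaction estimates will have wide intervals, and real predictors may be missed.
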